**6.5.3. Key objectives**

To achieve Specific Aim 5, the following key objectives are identified.

- Objective 1: To assess whether any of the biomarkers (PCA3 and TMPRSS2:ERG) are superior to the PCPT risk calculator (RC) for estimating the risk of prostate cancer.
- Objective 2: To assess whether any of the biomarkers (PCA3 and TMPRSS2:ERG) are superior to the 3-month finasteride PSA velocity for estimating the risk of prostate cancer.
- Objective 3 : To assess whether any of the biomarkers (PCA3 and TMPRSS2:ERG) are superior to the posterior risk calculated in Specific Aim 4 Equation (1) (i.e., a combination of PCPT RC and 3-month finasteride PSA velocity).
- Objective 4: To evaluate the independent predictive value of additional prostate cancer biomarkers including PCA3 and TMPRSS2:ERG and 3-month finasteride PSA velocity on the performance of the PCPT risk calculator.

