**6. Data Analysis**

**6.1 Statistical Considerations for the Study**

Statistical endpoints of the study and definitions of terms are first provided for reference for the statistical plan for Specific Aims 2-5. Lists of analysis plans and power calculations follow for the required sample size of 500 (144 expected cancer cases in finasteride arm; 216 expected controls in finasteride arm; 90 subjects in placebo arm; 10% inflation for drop-out).

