**Secondary endpoints**:

- 3-month finasteride PSA velocity in cases and controls.
- Operating characteristics of initial and 3-month finasteride PSA, DRE, PCA3, and TMPRSS2:ERG (TMPRSS2:ERG) for biopsy outcome.

Definitions:

- Intermediate risk: risk of prostate cancer between 20% and 60% using PCPT Risk Calculator.
- 3-month finasteride PSA velocity: monthly change in log PSA while on finasteride. Clinical PSA baseline value (obtained within 3 months period prior to enrollment) and Research PSA Baseline (first) value is immediately prior to finasteride.
- Baseline (initial) PSA (DRE, PCA3, and TMPRSS2:ERG): PSA (DRE, PCA3, and TMPRSS2:ERG) value immediately prior to randomization.
- 3-month finasteride PSA (DRE, PCA3, and TMPRSS2:ERG): PSA (DRE, PCA3, and TMPRSS2:ERG) value at 3 months after 3-month of finasteride.
- 3-month placebo PSA (DRE, PCA3, and TMPRSS2:ERG): PSA (DRE, PCA3, and TMPRSS2:ERG) value at 3 months after 3-month of placebo.
- Sensitivity: The proportion of cancer cases with marker value exceeding a cutoff (specific to the choice of cutoff selected).
- Specificity: The proportion of control cases with marker value at or below a cutoff (specific to the choice of cutoff selected). Equals 100%-False Positive Rate.
- ROC curve: A graph of 1-Specificity (i.e. False Positive Rate) on the x-axis by Sensitivity on the y-axis. The closer the curve comes to the 45-degree diagonal of the ROC space, the less accurate the test.
- AUC curve: Area underneath the ROC curve ranging from 0 to 1, higher AUC indicates a better marker. Because a completely random guessing produces the diagonal line between (0, 0) and (1, 1), which has an AUC of 0.5, no realistic classifier should have an AUC less than 0.5.

*Possible Pitfalls and Alternative Strategies*:

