**6.2.1. Power estimates for Specific Aim 2**

Sample size is selected to ensure sufficient accuracy for characterizing the operating characteristics (sensitivity and specificity) of 3-month finasteride PSA velocity and to have adequate power to detect the difference in PSA decline between cases and controls (non-cases). We estimate a positive biopsy rate of 40% in study subjects. Thus, the ratio of cancer cases to non-cases (controls) is 0.67(=0.4/0.6). With finasteride, a decline of 34% was seen in controls by 3 months[6]; a decline of 10-15% in cancer cases is assumed, corresponding to an additive change on a logarithmic PSA scale (in order to assume normality) of -log(1-0.34)=0.416 for controls, and -log(1-0.10)=0.105 to –log(1-0.15)=0.163 for cases. An estimate of the standard deviation of log PSA from the 3379 SABOR cohort is .89. Assuming a correlation of .5 between two PSA measures from the same patient (before and after finasteride) implies the same standard deviation for the difference or change in log PSA over 3-months. With these assumptions, a sample of 360 (144 cancer cases and 216 controls) in finasteride arm achieves a 75% to 90% power to test the null hypothesis that there is no difference between cases and controls in 3-month finasteride PSA change with a significance level (alpha) of 0.05 using a two-sided two-sample t-test (Table IX).

Table IX: Power for 216 Controls (no PCa) and 144 Cases (PCa) in Finasteride Arm

| PSA decline in | PSA decline in cancer cases | | | | |
| --- | --- | --- | --- | --- | --- |
| Controls | 8 % | 10% | 12% | 14% | 16% |
| 30 % | **.814** | **.747** | .665 | .574 | .479 |
| 32 % | **.884** | **.833** | **.766** | .687 | .598 |
| 34 % | **.934** | **.900** | **.851** | **.788** | .713 |
| 36 % | **.966** | **.944** | **.912** | **.867** | **.809** |
| 38 % | **.984** | **.973** | **.954** | **.926** | **.886** |
| 40 % | **.994** | **.988** | **.979** | **.963** | **.939** |

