**6.4.1. Analysis for Specific Aim 4**

Multivariable logistic regression will be used to ascertain whether 3-month finasteride PSA velocity adds independent diagnostic information for predicting cancer outcome on biopsy relative to the PCPT risk factors: PSA, DRE, family history and prior biopsy on this N=360 cohort. 3-month finasteride PSA velocity will be declared to add independent diagnostic information to the risk factors if it retains statistical significance at the 0.05 level when included in the multivariable logistic regression along with all other risk factors. This particular analysis may have limited power since the cohort is relatively small and several risk factors will be estimated.

An analysis with higher power is obtained by our recent methodology for incorporating a new marker from an external study into the PCPT risk calculator through computation of the likelihood ratio.[24] The likelihood ratio of 3-month finasteride PSA velocity will be defined as the ratio of probabilities of observing a specific 3-month finasteride PSA velocity value in cases relative to controls stratified by the PCPT risk factors. The probabilities will be modeled separately for cases and controls by linear regression with 3-month finasteride PSA velocity as outcome and covariates the PCPT risk factors: race, age, log PSA (before finasteride), DRE (before finasteride), family and prior biopsy history. By Bayes formula, an updated posterior odds of prostate cancer given 3-month finasteride PSA velocity and the PCPT risk factors is equal to the product of the likelihood ratio by the prior odds defined by the PCPT risk calculator. The posterior odds can be transformed into the posterior risk by posterior risk = posterior odds/[1+posterior odds]. (1)

Graphs of the posterior risk against the prior risk will be examined to assess the potential impact of 3-month finasteride PSA velocity as an additional risk factor to the PCPT risk factors.

*Potential pitfalls and alternative strategies for Specific Aim 4*

The standard deviations in the likelihood ratios may be high resulting in updated PCPT risks with large confidence bands (high uncertainty). These confidence bands will be displayed and reported. In this case, the need for further validation studies of 3-month finasteride PSA as a biomarker will be needed.

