**6.5.4. Analysis for key objectives**

- Objectives 1 to 3

Tests of differences in the AUC between all pairs of markers (Objective 1: PCPT RC vs. PCA3 and PCPT RC vs. TMPRSS2:ERG; Objective 2: PSA velocity vs. PCA3, PSA velocity vs. TMPRSS2:ERG; Objective 3: posterior risk vs. PCA3, posterior risk vs. TMPRSS2:ERG) will be performed using the U-statistic approach of DeLong et al.[67] Marker sensitivities will be compared at matched-specificities; marker specificities will be compared at matched-sensitivities. The same power calculation as for Specific Aim 3 applies.

- Objective 4

Multivariable logistic regression will be used to ascertain whether 3-month finasteride PSA velocity, PCA3 and TMPRSS2:ERG add independent diagnostic information for predicting cancer outcome on biopsy relative to the PCPT risk factors in this cohort. A new biomarker will be declared to add independent diagnostic information if it retains statistical significance at the .05 level when included in the multivariable logistic regression along with all other risk factors. This analysis may have limited power since the cohort is relatively small and several risk factors will be estimated.

In addition, the approach of Ankerst et al. (2008)[24] will be used to combine the predictive information of the new biomarkers. In Specific Aim 4, we plan to upgrade the PCPT risk calculator by including the 3-month finasteride PSA velocity. In Specific Aim 5, four types of updates of the PCPT risk calculator will be examined: 1) adding a single marker (PCA3, TMPRSS2:ERG, , or PSA velocity); 2) adding two markers at a time (6 possibilities); 3) adding three markers at a time (4 possibilities); and 4) adding all four biomarkers. In each case, likelihood ratios for the biomarkers will be modeled using normal distribution (for Type 1 update) or multi-normal distribution (for Type 2-4 updates) for inclusion of new biomarkers with means conditional on PCPT risk factors. The likelihood ratios will be multiplied by the prior odds of prostate cancer of the PCPT risk calculator to form the posterior risks of prostate cancer. Risk curves and surfaces will be examined to assess the potential impact of new biomarkers as additional risk factors to the PCPT risk factors for Type 1 update and Type 2-4 updates, respectively.

*Potential pitfalls and alternative strategies for Specific Aim 5*

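### Objective 3 of Aim 5 tests the urine markers against a posterior risk fitted to the same men's biopsy results, which inflates the comparator's AUC by roughly 0.03 and biases the DeLong test against the markers

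*Protocol*

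**What the plan says.** Protocol 6.4.1 (Aim 4) defines the posterior odds of cancer as the "product of the likelihood ratio by the prior odds defined by the PCPT risk calculator". The prior odds are external. The likelihood ratio is not: "The probabilities will be modeled separately for cases and controls by linear regression with 3-month finasteride PSA velocity as outcome", with covariates "race, age, log PSA (before finasteride), DRE (before finasteride), family and prior biopsy history". Section 6.1 gives the men available for this fit as "144 expected cancer cases in finasteride arm; 216 expected controls in finasteride arm".

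Protocol 6.5.3 makes the result the comparator in Objective 3: is either urine marker "superior to the posterior risk calculated in Specific Aim 4 Equation (1")? Section 6.5.4 fixes the pairs, "Objective 3: posterior risk vs. PCA3, posterior risk vs. TMPRSS2:ERG", and the test, which is DeLong's. It adds sensitivity and specificity comparisons at matched values. The pitfalls paragraph for Aim 5 counts Objectives 1 to 3 among those the study is designed to power adequately.

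The pitfalls paragraphs for Aims 4 and 5 mention wide confidence bands. Neither mentions optimism, and the protocol names no cross-validation, bootstrap correction or split sample.

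**The concern.** The two sides of the comparison are treated unequally. PCA3 and TMPRSS2:ERG are fixed-formula assay scores, so nothing about them is tuned to this trial's biopsies. The posterior risk is tuned to them, since its regressions are fitted separately by biopsy result and its AUC is then measured against those same results. DeLong's variance treats both quantities as markers given in advance. It allows neither for the upward shift in the fitted one nor for the uncertainty in its coefficients.

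At stake is whether a urine test does better than the calculator updated with the finasteride challenge. A marker that is truly better can fail to show it, and the updated calculator can look better than it would in new patients.

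**Working it through.** **Inputs from the protocol.** 144 cases and 216 controls (6.1). Prior risk: "risk of prostate cancer between 20% and 60% using PCPT Risk Calculator" (6.1, definitions). Fall in log PSA: "log(1-0.34)=0.416 for controls, and -log(1-0.10)=0.105", with 0.163 as the other value for cases (6.2.1). SD of change 0.89 and before/after correlation 0.5 (6.2.1).

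**The protocol's own figure first.** The difference in log PSA change is 0.416 - 0.163 = 0.253, or 0.416 - 0.105 = 0.311 (0.310 unrounded). The standard error is 0.89 x sqrt(1/144 + 1/216) = 0.0957. Power is about Φ(0.253/0.0957 - 1.96) = 0.75, and Φ(0.310/0.0957 - 1.96) = 0.90. This reproduces the stated 75% to 90%, so the inputs are read correctly. The protocol gives no AUC for the posterior risk.

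**Parameters fitted.** Each regression has 1 intercept, 6 slopes and 1 residual SD, which makes 8. Two regressions make 16, or 18 if race has three levels.

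**Simulation.** Each simulated trial has 144 cases and 216 controls. Velocity is given the mean difference and SD of the 3-month change, as in the protocol's power calculation. Both regressions are fitted and the posterior odds formed as in 6.4.1. The AUC in the same 360 men is compared with the AUC of the same fitted rule in 20,000 new men. Risk-factor distributions and calculator behaviour are assumed. Each scenario used 400 to 1,500 trials.

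| Scenario (SD 0.89 unless stated) | AUC, same men | AUC, new men | Optimism |
|---|---|---|---|
| Difference 0.253, change-baseline correlation -0.5 | 0.668 | 0.636 | 0.032 |
| Difference 0.311, correlation -0.5 | 0.680 | 0.651 | 0.029 |
| Difference 0.253 / 0.311, correlation 0 | 0.664 / 0.672 | 0.629 / 0.639 | 0.035 / 0.033 |
| Difference 0.253 / 0.311, three race levels | 0.671 / 0.681 | 0.635 / 0.649 | 0.036 / 0.032 |
| Velocity uninformative | 0.647 to 0.650 | 0.602 to 0.607 | 0.040 to 0.048 |
| Difference 0.311, SD 0.60 / 0.40 / 0.30 (assumed) | 0.710 / 0.767 / 0.822 | 0.690 / 0.752 / 0.814 | 0.020 / 0.015 / 0.009 |

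A second simulation gave about 0.02 to 0.03 at the protocol's effects and 0.046 with no velocity effect.

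**Effect on the DeLong test.** The marker was simulated as independent of the posterior risk given biopsy result. When its true AUC equals that of the fitted rule in new men, the mean z is -0.78 (difference 0.253) or -0.69 (0.311), where it should be 0. By the normal approximation:

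- Marker declared better: Φ(-0.78 - 1.96) = 0.003 and Φ(-0.69 - 1.96) = 0.004. Simulated: 0.6% and 0.5%. Nominal: 2.5%.
- Posterior risk declared better: Φ(0.78 - 1.96) = 0.12 and Φ(0.69 - 1.96) = 0.10. Simulated: 11.6% and 9.8%. Nominal: 2.5%.
- Marker truly 0.10 better: mean z is 1.76 or 1.85, against 2.54 or 2.59 with an unfitted comparator. Power is Φ(1.76 - 1.96) = 0.42 and Φ(1.85 - 1.96) = 0.46, against Φ(2.54 - 1.96) = 0.72 and Φ(2.59 - 1.96) = 0.74. Simulated: 42% and 45%, against 71% and 74%. The second simulation gave 43-50% against about 75%.
- Marker truly 0.08 better: simulated power 22% and 28%, against 52% and 54%.

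**Whether the remedy works.** In a further set of simulated cohorts, the AUC in the same men, by 10-fold cross-validation and in new men was 0.658 / 0.619 / 0.622 at a standardised difference of 0.253/0.89 = 0.284. It was 0.641 / 0.596 / 0.598 with no effect. At a standardised difference of 0.348, cross-validation gave 0.628 against 0.632 in new men. Cross-validation was therefore within 0.004 throughout.

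**The case against.** Several points on the other side are sound and limit the finding.

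- **Scope.** Whether a urine test could replace the challenge is tested directly by Objective 2, where velocity is each man's own regression slope and nothing is fitted to biopsy outcome. Objective 1 uses the external calculator. A reader might infer that all of Aim 5, or the primary endpoint, is biased, but the protocol's definitions rule that out.
- **Direction.** Objective 3 asks only whether a marker is superior. For that claim the bias is conservative, and its cost is lost power. The 10-12% error arises only if the result is read the other way, as the posterior risk beating the marker. Calling the test simply invalid goes too far. A two-sided comparison will still be read in both directions, and the power loss falls on an objective the protocol says is powered.
- **Size.** An inflation of 0.04 or more is tempting to quote, but it appears only when velocity carries no information. The SD of 0.89 is itself soft: it is a cross-sectional figure carried over to the change by assuming a correlation of 0.5. A smaller SD shrinks the inflation to 0.01-0.02.
- **Aim 4.** A reader might extend the point to the plots of posterior against prior risk, or to a claim that adding velocity beats the calculator. The plots are descriptive and carry confidence bands. Section 6.5.4 lists no DeLong comparison of posterior risk with calculator, and Aim 4 judges velocity by logistic regression and graphs.
- **SAP.** Internal validation is often left to the SAP, which is not shown, and the protocol leans on a cited method. But the protocol has itself named the comparator, the pairs and the test, and applied as written they give a biased comparison.

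It could also be said that the likelihood ratio might be fitted elsewhere, because 6.4.1 speaks of a marker from an external study. In context the trial is what is external to the PCPT, and the protocol names no other cohort with 3-month finasteride velocity.

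**Conclusion.** The concern stands for Objective 3 only. The comparator's AUC is inflated by roughly 0.03 at the protocol's effect sizes and SD of 0.89. Depending on the SD of change, the velocity effect, and the risk-factor distribution and calculator coefficients that had to be assumed, the range is about 0.01 to 0.05. An equally good marker is declared superior in about 0.5% of trials where 2.5% is nominal, and the posterior risk is declared better in about 10-12%. Power for a marker truly 0.10 better falls from about 70-75% to about 42-50%. These error rates assume SD 0.89 and a marker independent of the posterior risk given biopsy result. The direction of the bias was the same in every scenario run; its size is approximate. It should be corrected, though it does not touch the primary endpoint.

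**What to change.** In 6.5.4, state that for Objective 3 the AUC, sensitivity and specificity of the posterior risk will be computed from out-of-sample posterior risks, for example by repeated 10-fold cross-validation that refits both regressions in each fold, or will be bootstrap optimism-corrected. Take the confidence interval for each AUC difference from a bootstrap that repeats the whole fit, in place of the DeLong variance. Apply the same rule to the Type 1-4 calculator updates only if an AUC, sensitivity or specificity is quoted for them. The Aim 4 plots need no change.

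The cost is slightly more analysis work and a reported posterior-risk AUC lower by about 0.03. No extra participants, visits or samples are needed.

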**6.5.4. Analysis for key objectives**

- Objectives 1 to 3

Tests of differences in the AUC between all pairs of markers (Objective 1: PCPT RC vs. PCA3 and PCPT RC vs. TMPRSS2:ERG; Objective 2: PSA velocity vs. PCA3, PSA velocity vs. TMPRSS2:ERG; Objective 3: posterior risk vs. PCA3, posterior risk vs. TMPRSS2:ERG) will be performed using the U-statistic approach of DeLong et al.[67] Marker sensitivities will be compared at matched-specificities; marker specificities will be compared at matched-sensitivities. The same power calculation as for Specific Aim 3 applies.

- Objective 4

Multivariable logistic regression will be used to ascertain whether 3-month finasteride PSA velocity, PCA3 and TMPRSS2:ERG add independent diagnostic information for predicting cancer outcome on biopsy relative to the PCPT risk factors in this cohort. A new biomarker will be declared to add independent diagnostic information if it retains statistical significance at the .05 level when included in the multivariable logistic regression along with all other risk factors. This analysis may have limited power since the cohort is relatively small and several risk factors will be estimated.

In addition, the approach of Ankerst et al. (2008)[24] will be used to combine the predictive information of the new biomarkers. In Specific Aim 4, we plan to upgrade the PCPT risk calculator by including the 3-month finasteride PSA velocity. In Specific Aim 5, four types of updates of the PCPT risk calculator will be examined: 1) adding a single marker (PCA3, TMPRSS2:ERG, , or PSA velocity); 2) adding two markers at a time (6 possibilities); 3) adding three markers at a time (4 possibilities); and 4) adding all four biomarkers. In each case, likelihood ratios for the biomarkers will be modeled using normal distribution (for Type 1 update) or multi-normal distribution (for Type 2-4 updates) for inclusion of new biomarkers with means conditional on PCPT risk factors. The likelihood ratios will be multiplied by the prior odds of prostate cancer of the PCPT risk calculator to form the posterior risks of prostate cancer. Risk curves and surfaces will be examined to assess the potential impact of new biomarkers as additional risk factors to the PCPT risk factors for Type 1 update and Type 2-4 updates, respectively.

*Potential pitfalls and alternative strategies for Specific Aim 5*

As it is the primary focus, this study is mainly designed to have adequate power for Specific Aim 2 and 3, and the first three objectives of Specific Aim 5. The standard deviations in the likelihood ratios may be high resulting in updated PCPT risks with large confidence bands (high uncertainty). In this case, the observed data will assist us in planning a larger study in the future to further evaluate the independent predictive value of additional prostate cancer biomarkers and to improve the confidence interval estimations of the posterior risks of prostate cancer. A major advantage of this study design is that urine and serum samples will be reserved in the UTHSCSA biorepository. As biomarkers are discovered, it will be possible to retrospectively query study samples to address the same questions as are prospectively planned in this study for these new markers.

Appendix I
